## Abstract

Parents are often appointed a passive role in the care for their hospitalised child. In the family-integrated care (FICare) model, parental involvement in neonatal care is emulated. Parental participation in medical rounds, or family-centred rounds (FCR), forms a key element. A paucity remains of randomised trials assessing the outcomes of FCR (embedded in FICare) in families and neonates, and outcomes on an organisational level are relatively unexplored. Likewise, biological mechanisms through which a potential effect may be exerted are lacking robust evidence. Ten level two Dutch neonatal wards are involved in this stepped-wedge cluster-randomised trial FCR (embedded in FICare) by one common implementation strategy. Parents of infants hospitalised for at least 7 days are eligible for inclusion. The primary outcome is parental stress (PSS:NICU) at discharge. Secondary outcomes include parental, neonatal, healthcare professional and organisational outcomes. Biomarkers of stress will be analysed in parent–infant dyads. With a practical approach and broad outcome set, this study aims to obtain evidence on the possible (mechanistic) effect of FCR (as part of FICare) on parents, infants, healthcare professionals and organisations. The practical approach provides (experiences of) FICare material adjusted to the Dutch setting, available for other hospitals after the study.

## 1. Introduction

Due to the technological environment of the modern neonatal ward, it is a worldwide practice that preterm or ill infants and their parents are commonly separated, and both physical and emotional closeness are impaired [1]. Having an infant hospitalised in a neonatal intensive care unit (NICU) is a stressful experience for parents [2]. Parents are generally assigned a supportive role during the infant’s hospital stay [3]. As a result, many parents feel anxious, stressed and unprepared to care for their infants during hospitalisation and after discharge [1,4,5,6]. Specifically in the case of preterm delivery, the unexpected birth at a lower gestational age causes mothers to have less time for emotional preparation [7]. Parents experience more stress related to feelings of helplessness, exclusion, alienation, anxiety and depression [1,8]. These symptoms tend to persist after discharge and can affect the short- and long-term relationship with their infant [9,10]. Developmental research has firmly established the quality of the relationship between an infant and his or her parents as an important factor influencing the child’s later development. When children develop a secure and supported relationship with their parents or caregivers in the first years of life, they generally have better cognitive outcomes and better social interactions; they display fewer behavioural problems, and achieve better at school [11].

When examining sources of parental stress during admission of a critically ill infant, role alteration is found to be of great importance. The severe illness and the NICU environment inhibit parents from naturally growing into the new role of being or becoming a parent and parent–infant closeness is inhibited [12]. This can make them feel like a visitor instead of caregiver with feelings of helplessness about how to best support their infant during this stressful period [8]. By educating parents in their irreplaceable role and how to participate in neonatal care, healthcare professionals can help parents gain more confidence and reduce their levels of stress [13]. However, this close collaboration with parents is just starting to arise, and still needs to be implemented and integrated into work processes and culture of many NICUs and neonatal wards [12].

The family-integrated care (FICare) concept encourages and educates parents to provide the care for their infant as much as they are able and their confidence allows [14]. The FICare model is a collaborative program designed to support parents to cope with the distress that comes with their newborn’s hospital admission, based on four pillars: educating parents, educating healthcare professionals, peer-to-peer support and the unit environment. By empowering parents, the goal of FICare is to prepare them emotionally, cognitively, and physically to care autonomously for their infant at the time of discharge [15]. Parents are guided in their learning process as primary caregivers for their hospitalised infant by recognizing their valuable contributions and treating them respectfully as essential members of the care team, thus enhancing their sense of competence [16].

Healthcare professionals may experience a role change with the implementation of FICare, from being hands-on caregiver for the infant to becoming a coach for parents. In this collaboration, the care team is expanded with a “new” expert, i.e., the parent, who participates in the shared medical decision-making [17]. Education and support for the healthcare professionals provides them with the tools for coaching and adaptation to their new role.

Communication between healthcare professionals and parents in the neonatal ward has positive and negative effects on parents’ coping, knowledge, participation, parenting and satisfaction [18]. FICare aims to ameliorate parent–provider communication, which can have an effect on parental stress, by increasing the parents’ confidence and reducing their anxiety [18]. Regarding adequate communication, parental participation in medical rounds, also known as family-centred rounds (FCR), is a key element of the FICare concept [16,19].

Family-centred rounds include parents on medical rounds, aiming to involve them in the process of patient management. It allows parents to hear the development in their infants’ medical condition first-hand from the healthcare professionals and allows them to ask questions [20,21]. Even more important, parents can actively participate in the rounds to provide healthcare professionals with additional medical information on the current clinical state of their infant. Parents are excellent observers of their child, and often the most continuous factor in the care of their infant in the neonatal ward. Active participation in medical rounds is a logical next step and gives parents the opportunity to participate in shared decision-making.

The FICare model, including FCR, has been shown to improve neurodevelopmental outcomes in infants admitted to NICUs and level two neonatal wards in non-European settings [22,23,24]. This effect might be mediated by the reduction in parental stress levels caused by FICare during the neonatal period [22,25,26]. The underlying biological mechanisms of this reduced-stress response have not been previously investigated. Evidence is also not yet available on the effects of FICare in a European (Dutch) setting, differing from Canadian or American settings in many (logistic) ways. For example, many (relatively) smaller hospitals exist in the Netherlands and transfers of neonates between those hospitals are very common. Many healthcare professionals find it difficult to adjust the (extensive) FICare concept to their own setting. In order to prevent the emergence of great variations in FICare practice between hospitals, there is a need for a universal programme, adapted to the Dutch situation.

With the present study, we aim to investigate the effect of the implementation of FCR, incorporated into the FICare principles, on parental stress at discharge using a multicentre stepped-wedge cluster-randomised trial among parents of infants admitted to level two neonatal wards in the Netherlands. We hypothesise that the implementation of FCR embedded in FICare is superior to standard neonatal care without FCR with regard to the primary outcome. We will use a universal implementation strategy of FICare, adapted to the Dutch setting, to provide a practical approach for other Dutch hospitals after the study is concluded. Secondary outcomes include outcomes at the individual level in parents (longitudinal assessment of mental wellbeing) and infants (during the first year of life), and outcomes at the cluster level (effects on healthcare professionals, adherence to intervention and cost-effectiveness). Alongside, we aim to gain more insight into the underlying mechanism of the (expected) effect by measuring biomarkers of stress in parents and infants.

## 2. Materials and Methods

### 2.1. Patient Organisation Involvement

The Dutch patient organisation (Care4Neo) is actively involved in all stages of study, starting from the study design to the implementation of FICare in the participating hospitals, project evaluation and dissemination of the results. The Guideline for Reporting Involvement of Patients and the Public (GRIPP2 short form) is followed [27]. In the grant proposal, two representatives from Care4Neo ([name], [name]) were included in the project group, ensuring that the patient perspective and relevance were duly considered.

Regarding the study protocol and outcomes measured in the trial, a national survey was conducted together with Care4Neo to prioritise outcomes based on parents’ perspectives. The survey was disseminated through social media platforms of Care4Neo. Care4Neo was actively involved in the final selection of measurement methods and questionnaires. [name] and [name], together with Care4Neo’s Parent Advisory Board consisting of experienced parents, thoroughly reviewed the questionnaires, including explanatory texts, and provided input on how to inform parents about any abnormal scores on the questionnaires during study participation. Additionally, Care4Neo played a key role in revising the patient information forms. During the trial, Care4Neo is involved in the implementation of FICare by coordinating the peer-to-peer support programme in each participating centre.

### 2.2. Design

Due to the nature of the intervention, which involves changes to unit-level provision of care (medical rounds) and interaction between participants, there is a risk of cross-contamination. Therefore, to avoid contamination of patients and staff, the stepped-wedge cluster-randomised controlled trial design was selected. The trial is designed according to the CONSORT 2010 guidelines for stepped-wedge cluster-randomised controlled trials [28]. Randomisation will be performed using a random number generator, which will randomly assign the timing of start of intervention between sites. Hospitals will be stratified by level of care delivered (post-intensive care or not). The program will generate a series of blocks of varying sizes for each stratum and allocate units a time for intervention (3, 6, 9, 12 or 15 months, respectively) as is visualised in Figure 1.

### 2.3. Setting

In the Netherlands, the level of neonatal care is classified similarly to the structure provided by the American Academy of Pediatrics (AAP) [29]. Level 2 NICUs, also called special care nurseries, care for babies born at a gestational age of 32 weeks or more. These facilities are suited for babies who have moderate medical issues and are expected to recover fairly quickly. All the participating centres are level 2 neonatal wards. The average number of patients admitted to the neonatology department for more than 7 days per participating centre varies from 80 to 300 patients per year.

### 2.4. Study Population

In 2021, in the Netherlands, approximately 15% of (live) born infants were born preterm and/or small for gestational age, accounting for 25,018 infants [30]. According to Dutch policies, infants born with a gestational age < 32 weeks and/or birthweight < 1200 g or in need of intensive care (e.g., cardiorespiratory support) are born in/or treated at a NICU (level 3). In a Dutch level 2 neonatal ward, infants may receive non-invasive respiratory support, have central venous catheters and receive multiple medications. It is quite common for infants to be transferred between different hospitals prior to their final discharge to home.

In this paper, the intervention group will be referred to as the FICare-group and the control group as the standard neonatal care (SNC) group.

#### 2.4.1. Inclusion Criteria

Recruited patients will be patients admitted to a level 2 neonatal ward for 7 days or more. To be eligible to participate in this study, a subject (parent–infant dyad/triad) must meet all of the following criteria:−Infant requiring hospital admission directly (within 24 h) after birth;−Parent are 18 years or older;−Written, informed consent of both parents/legal guardians (compliant to the regulations of the Central Committee on Research Involving Human Subjects).

All healthcare professionals (nurses, nurse practitioners, residents, paediatricians and neonatologists) that are employed on the neonatal ward during the study are eligible to participate regarding healthcare professional outcomes.

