#### 2.4.2. Exclusion Criteria

A potential subject (parent–infant dyad) who meets any of the following criteria will be excluded from participation in this study:−Infant’s hospital stay shorter than 7 days;−Infant with severe congenital or syndromal anomaly;−Infant with critical illness who is unlikely to survive;−Parents with current severe psychosocial problems;−Involvement of child protective services in the family;−Parents not able or not willing to fill out questionnaires in English or Dutch.

Healthcare professionals of whom the employment in a participating centre is discontinued through the course of the study, will be excluded from further measurements.

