#### 2.9.1. Infant Outcomes

Infant outcomes include length of hospital stay, breastfeeding rates, growth, neurodevelopment at the (corrected) age of 12 months and saliva cortisol and buccal mucosal cells (see Section 2.9.5).

Neurodevelopment will be assessed using the Ages and Stages Questionnaire (ASQ, 3rd edition) [33]. With this tool, infant development can be assessed as reported by parents. The ASQ has been validated in a comparable population [34], and the validated Dutch version will be used for Dutch speaking participants [35]. The ASQ encompasses 5 domains: communicative, gross motor, fine motor, problem solving and adaptive skills. Each domain consists of 6 questions regarding the milestones that fit the age of the infant. Parents respond to the different items with “yes” (score = 10), “sometimes” (score = 5) or “not yet” (score = 0). For each domain, the score of the six items is summed, resulting in a domain score ranging from 0 to 60 and a total ASQ score with a maximum of 300 points. A positive screening is defined as scoring >2SD below the mean of the Dutch reference population in one domain, or scoring >1SD below the mean on more than one domain.

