#### 2.9.4. Cost-Effectiveness

Cost-effectiveness will be analysed at the level of families (medical and productivity costs), organisations (work absence, length of infant’s hospital stay, hospital care costs) and healthcare professionals (productivity costs).

The social aspect of cost-effectiveness will be assessed by both the Productivity Cost Questionnaire and the Medical Cost Questionnaire of the institute for Medical Technology Assessment (iMTA PCQ and iMTA MCQ) [58,59]. The questionnaires will be slightly adjusted to fit the paediatric setting, and parents will be asked to fill out these questionnaires at the (corrected) age of 12 months of their infant. Healthcare professionals will be asked to fill out the iMTA PCQ at start, halfway through and at the end of the study.

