#### 2.10.2. Statistical Analysis

All analyses will be performed based on an intention-to-treat principle to minimise attrition bias. A sensitivity analysis with a per protocol analysis, including, for instance, only the infants and families who have not been transferred from the study site to another hospital before discharge home, will also be performed. Possible bias due to differential withdrawal or study drop-out will be assessed in this per protocol sensitivity analysis as well. We will consider performing a subgroup analysis based on clinical characteristics, to adjust for differences in (severity of) infants’ medical conditions.

Baseline characteristics of the intervention and control group will be compared using student *t*-tests for continuous normally distributed variables, and Chi-square tests for categorical variables. Non-parametric tests will be used for variables that do not follow a normal distribution. Missing data will be handled by multiple imputation chain equations (mice) [70] with adjustment for clustering [71]. Rubin’s rules will be applied to pool the results of the different imputed dataset [72]. As described and proposed by the Panel on Handling Missing Data in Clinical Trials, we will carry out sensitivity analyses with different missing data strategies adjusted for clustering [73]. We will consider missing completely at random, missing at random, and missing not at random approaches.

With a generalised linear mixed modelling (GLMM) analysis, we will analyse whether parental stress at discharge is decreased after the intervention. We will include the factor “cluster” (hospital) as random effects, and “step” will be included as fixed (time) effect. In a secondary analysis, adjustment can be applied for possible confounders, such as (medical) characteristics of the infant during hospital stay. Adjustment for possible time effects will be made.

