Up till now, the effect of FICare on the physiological stress response in both infants and parents, using biomarkers of stress, has remained unexplored. It is known that psychological distress in lactating mothers during lactation can alter the composition of human milk regarding macro- and micronutrients, as well as the hormonal and immunological components [78,79,80]. Human milk is considered to improve infant health outcomes by facilitating the transmission of nutrients, hormones and cytokines from mother to child. The stress response is regulated to a great extent by glucocorticoids and previous research has shown that psychosocial interventions can affect cortisol levels in human milk [81]. However, the effect of interventions targeted on parental participation on such biomarkers of stress has not been described thus far. Therefore, the analysis of the cortisol levels in both human milk, hair and buccal saliva that are included in this trial might reveal answers and substantiate the beneficial effects of FICare on reducing stress.

Another novel evaluation includes a broad spectrum of the cost-effectiveness of FICare, beyond the evaluation of the infant’s length of stay [76]. Although reducing length of stay might evidently reduce healthcare costs, the effect of FICare on length of stay differs between studies [74,76,82]. The socio-economic effects of FICare, such as timing of resuming work by parents or work absence of healthcare professionals, have not been evaluated yet. By describing the cost-effectiveness, this study could guide hospital management to support implementation of FICare on their neonatal wards.

Changing hospital care culture and professional working methods, as occurs with implementing FICare, might impact healthcare professionals. Qualitative research evaluating the experiences of healthcare professionals with the FICare concept reveals that nurses indeed experience an alteration in their (professional) role, shifting from a professional caregiver to more of a supporting and educational role [83]. While nurses describe their new role as enhancing the parent–staff relationship, the process itself of changing might create challenges [17]. The effect of such interventions on the overall work pleasure and engagement in work of healthcare professionals remains unknown.

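### Eligibility depends on the actual stay (7 days or more), which FICare may change and which is also an outcome; the length-of-stay and hospital-cost effects will generally be attenuated if FICare shortens stay

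*Protocol article*

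**What the plan says.** Three places define eligibility by the stay that actually occurred.

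- Abstract: "Parents of infants hospitalised for at least 7 days are eligible for inclusion".
- Section 2.4.1: "Recruited patients will be patients admitted to a level 2 neonatal ward for 7 days or more".
- Section 2.4.2 excludes an infant with a "hospital stay shorter than 7 days".

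None refers to the stay expected at admission.

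The same variable is an outcome. Section 2.9.1 states: "Infant outcomes include length of hospital stay, breastfeeding rates, growth", and Table 1 lists length of stay in days at discharge. Section 2.9.4 includes the length of the infant's "hospital stay, hospital care costs" among the organisation-level components of the cost-effectiveness analysis.

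The Discussion (Section 4) notes that a shorter stay could lower healthcare costs, and that "the effect of FICare on length of stay differs between studies". It also says that FICare is open to all parents on the participating wards, not only to enrolled families.

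On analysis, Section 2.10.2 says: "All analyses will be performed based on an intention-to-treat principle to minimise attrition bias". The model has hospital as a random effect and step as a fixed effect. Adjustment for infant characteristics and a subgroup analysis by clinical characteristics are optional.

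**The concern.** In the intervention period a ward already works under FICare when an infant is admitted. Whether the infant reaches day 7 is settled afterwards, and FICare may influence it. An infant who would stay 7.5 days under standard care and 6.8 days under FICare is counted in the control phase and lost in the intervention phase.

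The two included groups then differ in two ways. The infants whose stay was brought below day 7 are missing from the intervention group. Those who remain are, on average, infants who would have stayed longer under standard care.

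Randomising the order of roll-out does not remove this, and neither does the step effect, because the selection changes with intervention status. Intention-to-treat among included families does not bring back infants who were never included.

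At stake is mainly the reading of a weak or null result on stay and hospital cost. It could come partly from the entry rule, while Section 4 expects the cost findings to inform hospital management.

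**Working it through.** The plan gives no figure to reproduce on this point, so the check is an illustration under stated assumptions.

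**Inputs from the document.** Threshold c = 7 days (Sections 2.4.1 and 2.4.2). PSS:NICU difference of 13 points = 0.5 SD (Section 2.10.1), so SD = 13 / 0.5 = 26.

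**Assumed inputs.** Stay among all admissions is lognormal with median m and log-SD s. FICare multiplies every stay by (1 - r). The correlation between stress and log stay is 0.2-0.4.

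**Formulas.** With a = (ln 7 - ln m)/s:

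- share reaching day 7 = 1 - Φ(a)
- mean stay given at least 7 days = m · exp(s²/2) · Φ(s - a) / [1 - Φ(a)]
- under FICare, replace m by m(1 - r)
- all-admissions effect = r · m · exp(s²/2)
- effect in infants eligible under standard care = r × their mean stay

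**Worked case: m = 8, s = 0.8, r = 0.10.**

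| Quantity | Control | Intervention |
|---|---|---|
| a | -0.167 | -0.035 |
| Share reaching day 7 | 57% | 51% |
| Mean stay given at least 7 days | 16.21 | 15.40 |

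- Filtered difference: 16.21 - 15.40 = 0.81 days.
- All-admissions effect: 0.10 × 8 × exp(0.32) = 1.10 days; retained 0.81/1.10 = 74%.
- Effect in infants eligible under standard care: 0.10 × 16.21 = 1.62 days; retained 0.81/1.62 = 50%.

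**Range at a 10% shortening, s = 0.6-0.8.**

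| Median of all stays | Retained, vs all admissions | Retained, vs infants eligible under standard care |
|---|---|---|
| 6-12 days | 58-80% | 37-67% |
| 20 days | 88-91% | 81-88% |

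The first comparator is the one a register analysis of all admissions would estimate.

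**Other shapes.**

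- Exponential stays, mean 15 days, 20% cut: by the memoryless property the filtered means are 15 + 7 = 22 and 12 + 7 = 19. The difference stays at 3.0 days, but the ratio moves from 0.80 to 19/22 = 0.864.
- Gamma stays with shape 0.8, same mean and cut: the filtered difference is slightly larger, 3.21 against 3.0 days.
- A fixed cut of 1 day with lognormal stays (s = 0.6): the filtered difference is only 0.04 days at median 8 and 0.57 days at median 20.

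**PSS:NICU.** Let z be the standardised log stay that the infant would have had under control care. Its mean among included infants is φ(a)/[1 - Φ(a)]. In the worked case this is 0.695 in control and 0.776 in intervention, a difference of 0.081.

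- If stress follows that latent stay, intervention scores rise by 26 × 0.2 × 0.081 = 0.42 to 26 × 0.4 × 0.081 = 0.84 points. Over medians of 6-20 days the range is about 0.2-1.3 points.
- If stress follows the actual stay, the difference in standardised log stay is ln(0.9)/0.8 + 0.081 = -0.132 + 0.081 = -0.051, and the stay-related difference in score is negative: 26 × 0.4 × (-0.051) = -0.53 at the upper correlation. Here the filter removes part of a stay-mediated reduction; it does not make included intervention families longer-stay families.

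**The case against.** **The bias is conditional and could be small.** It needs FICare to change stay, and Section 4 says that studies disagree. With a median near 20 days most of the effect survives, and with exponential stays the mean difference is untouched. All of this stands. It limits the size and rules out a flat statement that the effect is truncated towards zero. It does not remove the mechanism: Section 2.3 describes level 2 infants as likely to recover quickly, so stays near day 7 are plausible.

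**A reader might infer that the primary outcome is biased towards no effect because included intervention infants stay longer.** The documents do not support this. In the lognormal scenarios those infants have shorter actual stays; only the stay that they would have had under control care is longer. The shift is small against 13 points, and the direction of the stay-related difference depends on which of the two stays drives stress.

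**A reader might also infer a breach of intention-to-treat, with families removed after enrolment.** The article does not say when consent is taken, and Section 2.4.1 can be read as recruitment once day 7 is reached. Table 1 implies early contact only for infants born before 35 weeks. The conflict is not shown.

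**Judging expected stay at admission would avoid the problem.** That has its own price. Staff are unblinded, so a judged criterion could be applied differently in the two phases. Section 3.1 has all ten centres enrolling and completion expected by December 2023, so a change now would mix two definitions, unevenly across phases.

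**The optional adjustments in Section 2.10.2 bear on case mix.** They do, but they cannot restore the length-of-stay contrast.

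**Conclusion.** The concern holds in a limited form. As written, eligibility selects on a variable that is measured after exposure and is also an outcome, and no stated analysis repairs this. If FICare shortens stay, the effects on stay and hospital cost among enrolled infants will generally be understated. Under the lognormal assumptions with a 10% cut, about 58-80% of the all-admissions effect remains at medians of 6-12 days, and about 88-91% at 20 days. If FICare has no effect on stay there is no bias; if it lengthens stay, the selection reverses.

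The percentages rest on assumed distributions, because the document gives none. Any effect on the primary outcome is small and of uncertain direction, so it is not a reason to doubt the primary comparison. What is warranted is an inexpensive supplementary analysis and careful wording, not a change in eligibility.

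**What to change.** Keep the eligibility rule and add three things.

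1. **Supplementary analysis of stay and its hospital cost.** Use all ward admissions that meet the other criteria identifiable in the register, including infants transferred in from a level 3 NICU, without the 7-day filter. An aggregate extract by ward and quarter is enough, because the steps are 3 months long. Use the same cluster and step model as in Section 2.10.2. State whether stay means days on the level 2 ward or total hospital days, since Sections 2.4.1 and 2.4.2 word this differently and the two diverge for transferred infants.
2. **Selection check.** From the same extract, report the share of admissions reaching day 7 by ward and quarter. A fall after roll-out would indicate differential selection; in the worked case the share drops from 57% to 51%.
3. **Interpretation.** Describe the length-of-stay result in enrolled infants as conditional on a stay of at least 7 days.

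The cost is one small data extract per ward. It needs no new recruitment and can be done retrospectively. The drawback is that the all-admissions population differs from the enrolled one, so the two estimates answer different questions and should be presented side by side.
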